## Abstract

**Methods::**

This study is a large sample multicenter randomized controlled trial. Eight hospitals served as sub centers to recruit patients. A total of 258 patients are divided into Yaobitong group and celecoxib group according to the ratio of 1:1. Celecoxib or Yaobitong capsule was taken orally for 14 days. Patients will complete the trial after 3 months of follow-up, and independent statisticians who are blinded to random assignment will analyze the data using SAS 9.3 software. The primary outcome was the visual analogue scale (VAS) score after 14 days of treatment, and Japanese Orthopaedic Association (JOA), Oswestry Disability Index (ODI), and SF-12 will be regarded as secondary outcomes. Safety indexes will be recorded before and after treatment, and adverse events (AEs) will be recorded throughout this trial.

**Discussion::**

This study will evaluate the efficacy and safety of Yaobitong capsule in treating LDH. The experimental results will provide evidence support to treat LDH with Yaobitong capsule.

## 1. Introduction

Lumbar disc herniation (LDH) is a frequently occurring disease in orthopedics, which seriously endangers the physical and mental health of patients.^[1,2]^ Most of the protruding lumbar intervertebral discs compress the nerve roots of L5 and S1, resulting in typical symptoms of sciatica.^[3]^ One study suggests that patients who fail to respond to conservative treatment for 6 weeks meet the surgical indications.^[4]^ At present, although the surgical treatment schemes such as percutaneous endoscopic lumbar discectomy are gradually improved,^[5]^ conservative treatment is still the first choice considering the acceptability of surgical treatment and postoperative complications.^[6–8]^

A large number of meta-analysis and randomized controlled trials showed that acupuncture, massage, traditional Chinese medicine, epidural injections and non steroidal anti-inflammatory drugs have a clear curative effect on LDH, which provides an optional treatment scheme for patients.^[9–13]^ However, a network meta-analysis showed that the effect of oral Chinese medicine is lower than that of acupuncture and massage, but there is insufficient evidence to this conclusion for acute LDH.^[14]^ Recent animal studies have shown that Yaobitong capsule can inhibit the inflammatory response and neuropathy of herniated intervertebral disc.^[10]^ However, there are few clinical studies on the treatment of lumbar process with lumbago, and there is a lack of clinical evidence.

Guidelines of the North American Spine Society and the American College of Physiologists recommend celecoxib as the first-line treatment for acute LDH.^[15]^ Although celecoxib capsules are widely used in the treatment of low back pain, there is evidence that celecoxib does not completely cure these lesions.^[16]^ Moreover, celecoxib lacks sufficient evidence to prove their effectiveness in improving daily function. As we know, celecoxib also has adverse reactions. The most common adverse reactions are gastrointestinal reactions, which increases the risk of gastrointestinal bleeding and perforation.^[17]^ In addition, patients with cardiovascular disease may not be suitable for celecoxib.^[18–20]^ Therefore, this study compared Yaobitong capsule with celecoxib capsule to further confirm the efficacy and safety of Yaobitong capsule, which may provide optional oral drugs for patients with acute LDH.

## 2. Methods and Analysis

### 2.1. Study design

This study is a multi-center, randomized controlled trial with a superiority design. Subjects who met the inclusion conditions will be allocated to the experimental group and the control group in a ratio of 1:1. The experimental group will be treated with Yaobitong capsule and the control group will be treated with Celecoxib capsule. The subjects in the 2 groups have no other basic treatment, and the treatment period is 14 days and the follow-up period was 3 months. The trial process is shown in Figure 1. The study was officially launched on November 8, 2021, and is expected to be completed in February 2023. Eight medical institutions will complete this trial, including The First Affiliated Hospital of Tianjin University of traditional Chinese Medicine, Gansu Hospital of traditional Chinese Medicine, Henan Luoyang orthopedic hospital, Affiliated Hospital of Shanxi University of traditional Chinese Medicine, Dongzhimen Hospital of Beijing University of traditional Chinese Medicine, Shandong Pharmaceutical Biotechnology Research Center, Suzhou Hospital of traditional Chinese Medicine, and The First Affiliated Hospital of Hunan University of traditional Chinese Medicine.

**Figure 1. F1:**
[figure not shown]
The study flow chart. The flowchart of enrollment, interventions and analysis.

### 2.2. Ethics and registration

This study was approved by the ethics committee of Changchun University of traditional Chinese medicine on June 11, 2021 (Permission number CCZYFYLL2020 Shenzi-016-02), and is valid until June 11, 2023. We will follow the International Conference Guideline for Good Clinical Practice to ensure that the data and the results are credible. Before starting the study, Patients will be informed of the treatment plan and ethical approval number, and they have the right to know the intervention measures of the trial. Informed consent will be signed by the patients. The patients will sign the informed consent (see appendix 1) if they agree to participate in the clinical trial. This study is registered on September 22, 2020 with the Chinese Clinical Trial Registry, and the registration number is ChiCTR2000038405.

### 2.3. Patient recruitment

The study began to recruit patients on November 8, 2021. The first volunteer was recruited on November 29, 2021. It is expected to complete the patient recruitment in November 2022.Eight sub centers from different provinces in China participated in the implementation of the project. The First Affiliated Hospital of Tianjin University of traditional Chinese medicine, Gansu Hospital of traditional Chinese medicine, and Dong zhimen Hospital of Beijing University of traditional Chinese medicine were respectively responsible for the recruitment of 24 patients; Henan Luoyang orthopedic hospital, the Affiliated Hospital of Shanxi University of traditional Chinese Medicine and the First Affiliated Hospital of Hunan University of traditional Chinese Medicine were responsible for recruiting 36 patients respectively; Shandong Medical Biotechnology Research Center was responsible for recruiting 40 patients; Suzhou Hospital of traditional Chinese medicine was responsible for recruiting 38 patients. Each sub center will recruit volunteers through local advertising.

### 2.4. Eligibility criteria

#### 2.4.1. Diagnostic criteria.

The diagnostic criteria of LDH refer to an evidence-based clinical guideline for the diagnosis and treatment of LDH with radiculopathy and The diagnostic efficacy standard of TCM syndrome of the people’s Republic of China.^[9,21]^ The diagnostic criteria are as follows:

Medical history: with or without a definite history of lumbar injury.Symptoms and signs: low back pain radiates to buttocks and lower limbs, abdominal pressure increases, such as cough, sneezing, etc; There was tenderness and radiation to the lower limbs, and the lumbar movement was limited; There may be hypersensitivity or dullness in the affected innervated area of the lower limbs. Muscle atrophy may occur in patients with a long course of the disease. Tendon reflex and dorsiflexion of the toe may be weakened.Physical examination: positive muscle strength and sensation test; Straight leg raising or strengthening test was a positive result.Auxiliary examination: MRI showed LDH.

#### 2.4.2. Inclusion criteria.

The patient was aged between 18 and 70 years old. The clinical symptoms were leg pain extending below the knee, which was consistent with the corresponding nerve root distribution area of the MRI.The first course of low back pain or leg pain was less than 3 months, or the latest acute recurrence time was less than 3 months.This study will compare the efficacy and safety of Chinese patent medicine and Western medicine in the treatment of LDH.The VAS scores of leg pain were more than or equal to 4.0.

#### 2.4.3. Exclusion criteria.

The patient had a history of lumbar surgery.Patients have received oral or epidural steroid therapy in recent 3 months.Severe diabetes with peripheral neuropathy, severe osteoporosis, gastric ulcer, gastrointestinal bleeding, spinal tumor, spinal tuberculosis, spinal compression fracture.Allergic to non-steroidal drugs.There are symptoms of cauda equina nerve damage or parenchymal and progressive loss of motor function.Patients with litigation or legal claims.

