### 2.6. Intervention

The treatment regimen was divided into treatment and controlled groups according to randomization. The treatment group(T) was given oral Yaobitong capsules for 14 days. Usage and dosage: oral administration, 3 capsules each time, 3 times a day after meals. Main functions: promoting blood circulation and removing blood stasis, removing wind and dampness, promoting qi, and relieving pain. Indications: low back pain caused by blood stasis and qi stagnation and closed vein.

The controlled group (C) was given oral Celecoxib capsules for 14 days. Usage and dosage: oral administration, the recommended dosage is 400 mg for the first dose on the first day, which can be increased by 200mg if necessary, and then 200 mg twice a day according to the medication instructions.

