#### 2.8.3. Visit plan.

In this study, 8 visit points were designed (see Table 1), including day 0 before treatment (baseline, V1) and 5 visit points during 14 days of treatment (V2 ~ V6). The follow-up time points include month 1 (V7) and month 3 (V8). Each patient will complete all visits on the 3rd month. JOA, ODI, VAS, SF-12 scores will be collected at all interview points. Blood test, urine test, ECG, MRI, and X-ray will be collected at baseline and at the end of the treatment period on day 14. Adverse events (AEs) will be collected at all visit points (V2 ~ V8) during treatment and visit.

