### 2.10. Data collection and management

This trial uses a paper-based case report form (CRF) and an electronic data management system. The study staff will collect basic subject information, observational indicators, laboratory indicators, and AEs. Data collators will fill in the above data in the case report form and study medical record.

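### The Introduction cautions that patients with cardiovascular disease may not suit celecoxib, but the printed eligibility criteria contain no cardiovascular rule

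*Protocol article*

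**What the plan says.** All references are to the protocol article.

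- **Section 1 (Introduction)**, setting out the drawbacks of the comparator: "patients with cardiovascular disease may not be suitable for celecoxib".
- **Section 2.4.2 (Inclusion criteria)**: "The patient was aged between 18 and 70 years old". The other items concern symptoms, duration and pain score.
- **Section 2.4.3 (Exclusion criteria)**, by disease: "Severe diabetes with peripheral neuropathy, severe osteoporosis, gastric ulcer, gastrointestinal bleeding, spinal tumor, spinal tuberculosis, spinal compression fracture". A separate item reads "Allergic to non-steroidal drugs". The remaining items cover earlier lumbar surgery, recent steroids, cauda equina or progressive motor signs, and litigation.
- **Section 2.6 (Intervention)**: celecoxib for 14 days, starting with 400 mg, with 200 mg more on day 1 if needed, "and then 200 mg twice a day according to the medication instructions".
- **Section 2.8.3 (Visit plan)**: "Blood test, urine test, ECG, MRI, and X-ray will be collected at baseline and at the end of the treatment period on day 14". Baseline is V1, on day 0 before treatment.
- **Section 2.10 (Data collection and management)**: "The study staff will collect basic subject information, observational indicators, laboratory indicators, and AEs".

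**The concern.** The authors name a group of patients for whom the comparator may be unsuitable, then print an itemised eligibility list that does not deal with that group. The list does already screen for suitability for celecoxib in at least one respect, since the allergy item can hardly have another purpose. A cardiac test is also scheduled before treatment, yet nothing printed says what history or finding should keep a patient out.

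What is at stake is patient safety at entry. Without a common rule, eight centres may handle the same patient differently. The other safeguards in the article act only once dosing has begun: adverse events are collected from V2 to V8, the second ECG is on day 14, and events are reported to the ethics committee (sections 2.8.3 and 2.9).

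**Working it through.** **1. Could any printed text serve as a cardiovascular eligibility rule?**

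| Text | What it does | Keeps a patient out before randomisation? |
|---|---|---|
| Introduction, cardiovascular caution | Background on the comparator | No |
| 2.4.2, age limits | Admits ages 18 to 70 | No cardiovascular content |
| 2.4.3, disease exclusions | Names metabolic, bone, gastrointestinal and spinal conditions | No cardiovascular content |
| 2.4.3, allergy item | Screens for NSAID allergy | Yes, but for allergy only |
| 2.6, reference to medication instructions | Qualifies the celecoxib dose | No |
| 2.8.3, ECG at V1 | Schedules the test | No; no eligibility use is stated |
| 2.10, basic subject information | Collects data | No; no eligibility use is stated |
| 2.8.3 and 2.9, adverse events and day-14 ECG | Monitoring | No; these follow the start of dosing |

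No row supplies the rule.

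**2. The plan's own sample size.** Inputs from section 2.7: difference 0.5, SD 1.1, two-sided alpha 0.05, power 0.90, loss 20%.

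- A two-sample t-test calculation gives 102.68 per arm, rounded up to 103, so 2 × 103 = 206. This matches the article.
- Allowing for loss: 206 / (1 − 0.20) = 257.5, rounded up to 258. This also matches.

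**3. Effect of an added exclusion on these figures.** Patients are excluded before randomisation, so 206 and 258 do not change, provided the SD and difference still apply to the narrower population. Only screening grows. If a share p of otherwise eligible patients is removed, the number needed is 258 / (1 − p). The document gives no p, so these values are assumptions:

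- p = 1%: 258 / 0.99 = 260.6, so 261
- p = 5%: 258 / 0.95 = 271.6, so 272
- p = 20%: 258 / 0.80 = 322.5, so 323

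**4. How many patients might be exposed?** The celecoxib arm has 258 / 2 = 129 patients. The document gives no prevalence. If 1% to 20% of enrolled patients had any cardiovascular disease (assumed), the expected number in that arm would be 129 × 0.01 = 1.3 to 129 × 0.20 = 25.8. These are patients with any cardiovascular disease. How many of them would be unsuitable for celecoxib cannot be derived.

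**The case against.** **The article is a condensation.** The full protocol may contain a cardiovascular criterion. This stands as a limit on the finding: it is about the printed criteria. It does not dispose of the point, because the article prints an itemised list, down to litigation status, and that list does not address a caution which the same article states.

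**The caution is soft.** It says such patients may be unsuitable, and it appears in the rationale for studying another oral drug. It is compatible with case-by-case judgement by the investigator, and 14 days is a short exposure. This also stands, and it is why the point is modest. A reader might infer that the plan contradicts itself or gives patients a contraindicated drug. The document states no contraindication, so neither inference is supported.

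**The gastrointestinal exclusions prove little.** A reader might infer that the authors acted on one celecoxib risk and overlooked the other. The article gives no reason for excluding gastric ulcer or gastrointestinal bleeding. Only the allergy item clearly concerns suitability for the comparator, and it does not oblige the list to cover every other caution.

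**The size is unknown.** A reader could compute that, at an assumed 1% prevalence, the chance of at least one celecoxib patient having cardiovascular disease is 1 − 0.99^129 = 73%, and take this as the chance that an unsuitable patient is dosed. It is not: it rests on an assumed prevalence of any cardiovascular disease and says nothing about unsuitability or harm.

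**An ECG-based exclusion would be loose.** Excluding for a clinically significant ECG abnormality would leave an undefined judgement to each site and go beyond the Introduction, which speaks of disease and not of ECG findings. This stands, and the fix therefore gives the ECG a supporting role only.

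**Conclusion.** The point holds for the criteria as printed. The Introduction cautions against celecoxib in patients with cardiovascular disease, no eligibility item covers them, and no other printed text does that work before randomisation. Such patients up to age 70 can therefore be allocated to 14 days of celecoxib.

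It is a modest safety matter that should be corrected because the correction is simple. The conclusion assumes that the unseen full protocol adds no cardiovascular criterion. The number of patients affected is not derivable. A reader might go further and suspect a biased safety comparison or a distorted day-14 pain result; nothing in the document supports either, and neither is claimed.

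**What to change.** Add to section 2.4.3, for every patient before randomisation and whatever the later arm: *Known cardiovascular disease for which the celecoxib medication instructions advise against use, established from medical history.* State that the V1 ECG is read before randomisation as supporting information, and do not make it a separate exclusion. The instructions themselves are not among the documents, so the sponsor should list the relevant conditions for the sites to make the rule uniform.

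**Cost.**

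- One eligibility line, one history item and a notice to the sites. The ECG is already scheduled, but it must be read earlier than the article now requires.
- An ethics amendment during recruitment. The first volunteer was recruited on November 29, 2021 (section 2.3), so patients would have entered under two rules, and this should be reported.
- Slightly more screening, as worked above, with the sample size unchanged.
- Results that do not cover patients unsuited to celecoxib.

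If recruitment has closed (section 2.3 expected November 2022), an amendment no longer helps. The trial report should then state how cardiovascular disease was screened and how many patients with it were enrolled in each arm.

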### 2.5. Randomization and blinding

This study will apply the central randomization method by using the interactive Web response system to randomly assign the subjects to any group. The personnel providing the random sequence do not participate in the implementation of the whole trial. All clinical trial researchers evaluating outcomes can only get random numbers to assign patients by using computer, and neither the researchers nor the patients know which group the patients will be assigned. The independent statisticians will be blinded to random assignment.

### 2.6. Intervention

The treatment regimen was divided into treatment and controlled groups according to randomization. The treatment group(T) was given oral Yaobitong capsules for 14 days. Usage and dosage: oral administration, 3 capsules each time, 3 times a day after meals. Main functions: promoting blood circulation and removing blood stasis, removing wind and dampness, promoting qi, and relieving pain. Indications: low back pain caused by blood stasis and qi stagnation and closed vein.

The controlled group (C) was given oral Celecoxib capsules for 14 days. Usage and dosage: oral administration, the recommended dosage is 400 mg for the first dose on the first day, which can be increased by 200mg if necessary, and then 200 mg twice a day according to the medication instructions.

### 2.7. Sample size

This study is a randomized controlled trial with parallel control and superiority design. According to previous literature, the VAS score of the control group (celecoxib capsule) after treatment was 5 points.^[22–27]^ It is expected that after 2 weeks of treatment, the difference between the experimental group (Yaobitong capsule) and the control group is 0.5 points, and the standard deviation of the 2 groups is the same (standard deviation = 1.1). It was hypothesis *α* = 0.05 (bilateral), 1-*β* = 0.90. According to the calculation of PASS 11 software, at least 206 cases were collected in this study. Assuming a loss of follow-up rate of 20%, 258 patients need to be included in this study.

### 2.8. Outcome measurements

#### 2.8.1. Primary outcome.

VAS (visual analogue scale) score of leg pain on the 14th day of treatment was the main evaluation index of curative effect. VAS adopts a 10 cm scale divided into 1 to 10 points, of which 10 points are the maximum pain and 0 points are painless.^[28]^ Patients choose the score according to the degree of leg pain, which is the VAS score to evaluate the degree of pain.

#### 2.8.2. Secondary outcome.

Oswestry disability index (ODI) was used to assess dysfunction. The ODI has 10 main items, including 60 sub-items, to evaluate dysfunction from multiple dimensions.^[29]^ The lower the score, the lower the degree of functional restriction, and vice versa.

Japanese Orthopaedic Association (JOA) was used to assess dysfunction and degree of improvement.^[30]^ The JOA total score is 29 and the lowest is 0. The lower the score, the more obvious the dysfunction. The improvement index and improvement rate were used to assess the degree of improvement after treatment.

Improvement index = post-treatment score - pretreatment score.

Improvement rate = [(post-treatment score - pretreatment score)/ 29 - pretreatment score] × 100%.

SF-12 scale is a simplified version of SF-36, which contains 12 items with a full score of 100 to evaluate the physiological and psychological status of patients.^[31]^ The higher the score, the better the patient’s quality of life.

Secondary outcomes included the ODI score, JOA score, and SF-12 score of all visits. In addition, VAS scores at other visit times were also secondary outcomes. All visit points and evaluation indexes are presented in Table 1.

**Table 1 T1:** Visit plan.

Time	0th d(baseline)	1st d	3rd d	5th d	7th d	14th d	1st mo	3rd mo
Visit	V1	V2	V3	V4	V5	V6	V7	V8

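### The JOA improvement-rate formula in section 2.8.2 lacks brackets around its denominator and, evaluated as printed, does not measure improvement (minor; most likely a notation slip)

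*Protocol article*

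**What the plan says.** Section 2.8.2 of the protocol article describes the JOA scale by its range, "The JOA total score is 29 and the lowest is 0", and its direction, "The lower the score, the more obvious the dysfunction". Higher is therefore better, and 29 is the best attainable score.

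It then names two derived measures and their purpose: "The improvement index and improvement rate were used to assess the degree of improvement after treatment". The first is a simple change, "Improvement index = post-treatment score - pretreatment score". The second is "Improvement rate = [(post-treatment score - pretreatment score)/ 29 - pretreatment score] × 100", followed by a percent sign.

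The same section lists the secondary outcomes: "Secondary outcomes included the ODI score, JOA score, and SF-12 score of all visits", with VAS at the remaining visits. The improvement rate is not itself in that list. The formula appears nowhere else in the article, so nothing restates or corrects it.

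**The concern.** A rate of improvement on a scale with a ceiling is naturally the gain divided by the room left to gain. It should be 0% with no change and 100% on reaching the ceiling. The printed line has round brackets around the gain and square brackets around everything, but none around the two terms that should form the denominator. Division binds before subtraction, so only 29 divides the gain, and the baseline score is then subtracted whole.

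If that line were coded as it stands, the output would mostly report where patients started. JOA is collected at all eight visits (Table 1), so the same fault would carry into every post-baseline visit at which the rate is calculated.

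**Working it through.** **Inputs**, all from section 2.8.2: JOA range 0 to 29; higher is better; the printed formula. The article gives no numerical result for the rate, so there is no figure of its own to reproduce.

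**Formulas**, with *pre* and *post* for the two scores:

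- As printed: [(post - pre)/29 - pre] × 100 = 100 × (post - 30 × pre)/29.
- Denominator bracketed: 100 × (post - pre)/(29 - pre).

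**Sign.** Post cannot exceed 29. If pre is at least 1, then post - 30 × pre is at most 29 - 30 = -1. The printed value is therefore at most -100/29 = -3.4%, and always negative. At pre = 0 both forms reduce to 100 × post/29 and agree.

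**Weights.** In the printed form, one post-treatment point adds 100/29 = 3.4 percentage points. One baseline point subtracts 3000/29 = 103.4. The ratio is 30 to 1.

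**Values.**

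| Pre | Post | As printed | Bracketed |
|---|---|---|---|
| 0 | 10 | 34.5% | 34.5% |
| 1 | 29 | -3.4% | 100.0% |
| 10 | 10 | -1000.0% | 0.0% |
| 10 | 20 | -965.5% | 52.6% |
| 15 | 22 | -1475.9% | 50.0% |
| 20 | 25 | -1982.8% | 55.6% |
| 20 | 29 | -1969.0% | 100.0% |

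For example, 15 to 22 as printed is 100 × (22 - 450)/29 = -1475.9; bracketed, it is 100 × 7/14 = 50.0.

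**Ranking.** A patient who worsens from 10 to 5 gets 100 × (5 - 300)/29 = -1017.2%. A patient who recovers fully from 15 to 29 gets 100 × (29 - 450)/29 = -1451.7%. The printed rate ranks the first above the second.

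**Between groups.** The difference in mean printed rate is 3.4 × (difference in mean post score) - 103.4 × (difference in mean baseline score). A 3-point advantage in post score contributes 3 × 100/29 = 10.3 percentage points. A baseline difference of only 0.1 point contributes the same amount, 0.1 × 103.4 = 10.3.

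**Illustration under assumed distributions.** The article gives no JOA means or standard deviations. In a simulation assuming a baseline mean of 12 (SD 2 to 4) and a mean change of 7 (SD 4 to 6), the printed rate correlated -0.995 to -0.999 with baseline and only 0.06 to 0.12 with the actual change.

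**Reach.** The sample size in section 2.7 rests on VAS ("the difference between the experimental group (Yaobitong capsule) and the control group is 0.5 points", SD 1.1) and does not use the JOA rate.

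**The case against.** The best reply is that nobody would be misled. Section 2.8.2 gives the ceiling of 29 and the direction of the scale, and calls the quantity a rate in percent. With those facts, the gain over (29 - pretreatment score) is the only sensible reading, and a value of -1000% for an unchanged patient would be noticed on first output. Pre and post scores are recorded anyway, so the rate can be recalculated correctly at any time. This stands as far as severity goes. It does not make the printed line right: a stated outcome formula should not depend on the reader repairing it.

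Typesetting might also have flattened a stacked fraction. That cannot be excluded, but it is unlikely, because both other pairs of brackets on the line survived.

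A reader might infer more than the article supports, in three ways:

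- *That group differences would reflect baseline imbalance and not treatment.* Allocation is randomised 1:1, so the expected baseline difference is zero. The expected group difference in the printed rate is still 3.4 times the treatment effect on the post score. The fault is loss of precision and interpretability, not systematic bias.
- *That this is the plan's measure of JOA improvement.* Two are named, and the other, the improvement index, is correctly defined.
- *That the analysis will be programmed wrongly.* The article does not show how the rate is coded.

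**Conclusion.** The formula is wrong as printed and cannot serve the purpose section 2.8.2 gives it. The sign and weight results follow from the stated 0 to 29 range alone; only the simulated correlations rest on assumed distributions. The size of the error depends on baseline: there is none at 0, it can leave values only slightly negative at 1, and it runs to hundreds or thousands of percentage points at higher scores.

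The severity is minor. The slip has an evident intent and is confined to one derived measure of a secondary scale, outside the listed secondary outcomes. It does not reach the raw JOA score, the improvement index, the primary day-14 leg-pain VAS or the sample size, so it gives no reason to doubt the trial's main comparison.

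**What to change.** In section 2.8.2, state: Improvement rate = (post-treatment score - pretreatment score) / (29 - pretreatment score) × 100%. Add that the rate is undefined for a baseline of 29, where the denominator is zero. Confirm that the analysis program uses this expression; a quick test is that no change returns 0% and reaching 29 returns 100% from any baseline below 29. The cost is one pair of brackets and one sentence, with no change to data collection, visits or sample size.
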